## Materials and methods

Figure 1 presents a study flowchart. Only incident patients with an indication for RRT will be recruited. The study is intended to describe current practices of RRT in all patients admitted to ICUs who are in need of RRT, with or without ARF. All data listed herein will be entered in electronic case report forms (CRFs) that are available via the internet [11]. The following rules will be applied without exception:

First, all patient data will be entered anonymously. To this aim, each centre will have a code, and patients will be consecutively assigned a unique number. Under no circumstances will there be any written or oral transmission of data that may make it possible to identify any patient. Failure to adhere to this will be followed by cancellation of the data from the website by the webmaster.

Second, data for each patient will be entered in a separate CRF. These data may be copied from paper CRFs in order to make the reporting of data from bed to computer station easier. All fields may be amended at any time until the patient's CRF is completed and closed. At this point, one may access the patients' CRF but it will be no longer be possible to amend the CRF. In the case of overt inconsistency, corrections must be detailed in writing (e-mail) by the person responsible for data quality for the centre or by the center itself. In all cases, no corrections will be permitted in the absence of an express written request. The person responsible for data quality will have access to the centre's CRF in printed form only. A registry will collect correspondence between the person responsible for data quality and the centre.

Third, completion of some fields in the CRF is mandatory. Failure to complete them will prevent progression to the following CRF and closure of the opened CRF. Failure to complete a CRF electronically will result in the patient being excluded from the study.

Finally, Each centre will be able to open CRFs for its own patients but never CRFs for patients from other centres.

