#### Case report form: Admission (step 1)

This CRF will automatically provide the patient's consecutive number. The user must enter the following data:

• sex,

• date of birth,

• weight,

• height,

• date/time of hospital admission,

• premorbid plasma creatinine levels,

• date/time of ICU admission,

• diagnosis at admission,

• Simplified Acute Physiology Score (SAPS) II (the index will be automatically calculated once each requested field is completed),

• Sequential Organ Failure Assessment (SOFA; the index will be automatically calculated once each requested field is completed).

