#### Case report form: Criteria to initiate RRT (step 2)

This CRF will automatically provide the patient's consecutive number. The user must enter the date and time when the following clinical events (indexed numerically) occurred:

• 1. Oliguria (urine output <200 ml/12 hours),

• 2. Anuria (urine output <50 ml/12 hours),

• 3. High urea/creatinine,

• 4. Hyperkalaemia (>6.5 mmol/l or rapidly rising potassium),

• 5. Metabolic acidosis,

• 6. Fluid overload,

• 7. Hyperthermia (>41°C),

• 8. Immunomodulation,

• 9. What RIFLE (Risk Injury Failure Loss of function End stage renal disease) criteria [12] are applicable?

• 10. Others (to specify)

The user will also be asked to prioritize the criteria (from 1 to 3) when two or more specified. In addition, the modality chosen must be specified (defined as following and indexed numerically)

• 1. CVVH (as defined as ≤ 35 ml/kg per hour ultrafiltration rate in postdilution or <40 ml/kg per hour in predilution),

• 2. CVVHDF (defined as use of dialysate + replacement [define]),

• 3. High volume haemofiltration (defined as >35 ml/kg per hour in postdilution or >45 ml/kg per hour in predilution),

• 4. Pulse high volume haemofiltration (from 85 ml/kg per hour to 100 ml/kg per hour for 6–8 hours, followed by CVVH at 35 ml/kg per hour),

• 5. Coupled plasma filtration adsorption (CPFA) plus CVVH ,

• 6. IHD ('intermittent' includes conventional haemodialysis and slow extended daily dialysis, thereby encompassing all treatments in which sessions are separated from one another for 10 hours or more).

The CRF will then permit the user to specify any other relevent criteria, including the following:

• Staff problems,

• Technical problems,

• Product (e.g. fluids, lines, filters, machine) availability problems,

• Logistics,

• Others (to be specified).

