#### Case report form: Modality-specific assessment time (step 3)

On the basis of the modality chosen in the 'Criteria to initiate RRT' CRF (see above), a specific CRF will be opened. The CRF for IHD will require data entry at baseline, at 4 hours and at treatment end. The CRF will automatically indicate the different visits (i.e. 0.0, 4.0, and treatment end). The CRF for **IHD **will request the following information:

• Decision taken (date/time),

• Start (date/time),

• Prescribed duration (only at assessment time 0),

• Delivered duration,

• Prescribed blood flow rate (only at assessment time 0),

• Delivered blood flow rate,

• Total weight loss (kg/session),

• Type of haemodialyzer (specify only commercial name),

• Surface of haemodialyzer (m^2^),

• Type of buffer (code number for lactate or bicarbonate),

• Anticoagulation (code number for heparin, citrate, prostacyclin, saline flushes, no anticoagulation),

• Arterial site of vascular access (code number for radial, femoral, pedidial, axillary access),

• Venous site of vascular access (code number for subclavian catheter, femoral catheter, jiugular, axillary catheter),

• Type of vascular access (code number for double lumen catheter, single lumen catheter),

• Vascular access gauge,

• Treatment interrupted (date/time),

• Resumption of treatment (specify date/time),

• End (day/time),

• Change in modality.

The CRF for **CVVH **will require data entry at 0 hours, at 1 hour, 3 hours, 6 hours, 12 hours, 24 hours, and every 24 hours thereafter and at treatment end. The CRF will automatically indicate the different assessment times (i.e. 0.0, 1.0, 3.0, 6.0, 12.0, 24.0, and so forth). Assessment times at 1.0, 3.0, 6.0 and 12.0 are optional, while assessment time at 24.0 and for multiples of 24 are mandatory. The following information will be requested:

• Decision taken (date/time),

• Start (date/time),

• Prescribed duration (only in assessment time 0),

• Delivered duration,

• Prescribed blood flow rate (only in assessment time 0),

• Delivered blood flow rate,

• Prescribed effluent (ml/hour; only at assessment time 0),

• Total effluent (ml/24 hours; only at assessment time 24 or last assessment time before treatment interruption/end),

• Prescribed reposition rate (ml/hours; only at assessment time 0),

• Total reposition (ml/24 hours; only at assessment time 24 or last assessment time before treatment interruption/end),

• Total volume removed from the patient (ml/24 hours),

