• Delivered duration (hours; only at assessment time 24 or last assessment time before treatment interruption/end),

• Prescribed blood flow rate (ml/min; only at assessment time 0),

• Prescribed effluent (ml/hour; only at assessment time 0),

• Delivered effluent (ml/ 24 hour; only at assessment time 24 or last assessment time before treatment interruption/end),

• Prescribed reposition rate (ml/hour),

• Delivered reposition rate (ml/24 hours; (only at assessment time 24 or last assessment time before treatment interruption/end),

• Dialysate (ml/24 hours; only at assessment time 24 or last assessment time before treatment interruption/end),

• Total volume removed from the patient (ml/24 hours; only at assessment time 24 or last assessment time before treatment interruption/end),

• Type of haemodialyzer (as above),

• Surface (m^2^),

• Type of buffer,

• Anticoagulation (as above),

• Arterial site of vascular access (as above),

• Venous site of vascular access (as above),

• Type of vascular access (as above),

• Vascular access gauge,

• Treatment interrupted (date/time),

• Resumption of treatment (specify date/time),

• End (day/time),

• Change of modality.

Independently of modality chosen, all 'Modality-specific assessment time' CRFs include the following additional fields:

• SOFA (full set of data; only at assemement time 24 and for multiples of 24),

• Creatinine,

• Urea,

• Na,

• K,

• White blood cells (10^3^/μl),

• Platelets (10^3^/μl),

• Hb,

• pH,

• PaO_2_,

• PCO_2_,

• Bicarbonate,

• FiO_2_,

• Body temperature,

• Urine volume,

• Fluid balance (only at assessment time 24),

• Bicarbonate,

• Fractional inspired oxygen,

• Urine volume (ml/24 hours),

• Fluid balance (ml/24 hours),

• Systolic blood pressure (mmHg),

• Diastolic pressure (mmHg),

• Mixed venous oxygen saturation,

• Heart rate,

• Cardiac output,

• Cardiac index

• Pulmonary artery pressure,

• Systemic vascular resistance index,

• Intravascular blood volume index,

• Extravascular lung water index,

• Stroke volume variation,

• Vasopressor administration (milligrams of vasopressors/previous 24 hours): adrenaline (μg/kg per min), noradrenaline (μg/kg per min), dobutamine (μg/kg per min), dopamine (μg/kg per min), vasopressin (units/previous 24 hours), terlipressin (mg/previous 24 hours),

• Vasodilator administration,

• Other treatments: steroids (mg/24 hours; specify what type), recombinant human activated protein C, antithrombin III, protein C,

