## Discussion

The practice of CRRT has been subject to much debate. Only a few prospective randomized studies have been performed and published on the relationship between CRRT and outcome, and so conclusions are difficult to draw [20,21]. As emphasized in a recent editorial [22], in the field of artificial organs, prospective observational studies, despite their inherent limitations, have been performed because they are more affordable but are also capable of providing useful information from practical and medical standpoints.

Guerin and coworkers [23] studied 587 patients requiring haemodialysis and followed them until hospital discharge. Among the 587 patients, 354 received CRRT and 233 intermittent RRT as first choice. CRRT patients had a greater number of organ dysfunctions on admission and at the time of ARF, as well as higher SAPS II. Mortality was 79% in the CRRT group and 59% in the intermittent RRT group. Logistic regression analysis showed decreased patient survival to be associated with SAPS II on admission, oliguria, admission from hospital or emergency room, number of days between admission and ARF, cardiac dysfunction at time of ARF, and ischaemic ARF. No underlying disease or nonfatal disease, and absence of hepatic dysfunction were associated with an increase in patient survival. The type of RRT was not significantly associated with outcome. Those authors concluded that RRT mode was not of prognostic value.

The largest observational study ever performed (the BEST Kidney) was recently completed and reported in part [24]. A total of 1743 consecutive patients, who either were treated with RRT (CRRT or IHD) or fulfilled predefined criteria for ARF, were studied. Importantly, the findings indicated a marked difference in mortality rates across the different ICUs, suggesting that the practice of RRT may yet exert an influence on mortality [[name], unpublished observation]. Increasing the dose to 35 ml/kg per hour would be associated with a significantly greater survival in all ARF patients. However, higher dialysis doses (45 ml/kg per hour) had no statistically significant impact in the ARF patients studied. However, in a subgroup analysis including only those patients with sepsis, there was a trend suggesting that this might be the case.

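### No composite severity score is scheduled at the start of renal replacement therapy (RRT), and the SOFA field on the intermittent haemodialysis (IHD) form has no visit at which it can be completed

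*Protocol article*

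**What the plan says.** All references are to the protocol article.

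- **Who enters.** Materials and methods: "Only incident patients with an indication for RRT will be recruited". No time zero for study entry is fixed.
- **Admission form (step 1).** Both scores are requested: "Simplified Acute Physiology Score (SAPS) II (the index will be automatically calculated once each requested field is completed" and "Sequential Organ Failure Assessment (SOFA; the index will be automatically calculated once each requested field is completed". The SOFA item states no scoring window.
- **Criteria to initiate RRT (step 2).** This form takes dated clinical triggers and asks "What RIFLE (Risk Injury Failure Loss of function End stage renal disease) criteria [12] are applicable". It lists neither SAPS II nor SOFA.
- **Modality-specific assessment time (step 3).** The additional fields apply whatever the modality. SOFA is among them, restricted as follows: "SOFA (full set of data; only at assemement time 24 and for multiples of 24".
- **Visits on the step 3 forms.** CVVH, CVVHD and CVVHDF have a time 0 visit, optional early visits, and mandatory visits at 24 hours and its multiples. For intermittent treatment: "The CRF for IHD will require data entry at baseline, at 4 hours and at treatment end".
- **Outcome form (step 4).** SAPS II and SOFA are taken again over the 24 hours before ICU discharge.

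**The concern.** The study is observational, and its stated ultimate goal is to learn how the dialysis dose actually delivered affects patient outcome. The decision to start RRT is left to the attending physician. How ill a patient is when RRT starts is therefore an obvious potential confounder of the relation between dose and mortality, and it should be measured before the dose is given.

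On the printed schedule, the only composite scores near that moment are the admission score, which may be out of date by then, and the 24-hour SOFA. Adjusting for the 24-hour score risks removing part of the effect under study, because the dose may already have changed it. It also drops patients who die or stop treatment before 24 hours.

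The article itself gives a reason not to rely on admission scores alone. The cohort of 587 patients described in the Discussion linked poorer survival to admission SAPS II and oliguria, but also to "number of days between admission and ARF, cardiac dysfunction at time of ARF, and ischaemic ARF". Time elapsed since admission and organ function when renal failure occurred carried information of their own.

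**Working it through.** The article states no figure on this point, so there is nothing to recompute. The check sets the forms side by side.

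| Form and time | SOFA | SAPS II | Single physiological variables |
|---|---|---|---|
| Admission (step 1) | yes | yes | as needed for the scores |
| Criteria to initiate RRT (step 2) | no | no | RIFLE class, dated triggers |
| CVVH, CVVHD, CVVHDF at time 0 | no | no | yes |
| CVVH, CVVHD, CVVHDF at 24 h and multiples | yes | no | yes |
| IHD at 0 h, 4 h and end | no | no | yes |
| Outcome (step 4) | yes | yes | creatinine, urea |

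1. **Time 0.** The word *only* in the SOFA rule excludes time 0 on every step 3 form. Step 2 does not fill the gap.
2. **Early end of continuous treatment.** Several delivered-dose fields on the continuous forms may be completed at the last assessment before an interruption or end, if that comes before 24 hours. The SOFA rule has no such fallback, so a continuous treatment that ends before 24 hours yields no SOFA.
3. **IHD.** The additional fields belong to all step 3 forms, so the IHD form carries a SOFA field. Its visits are 0 hours, 4 hours and treatment end. Step 2 defines intermittent treatment by gaps of at least 10 hours between sessions, so a session given daily lasts at most 24 − 10 = 14 hours. Even if several sessions were logged as one continuing treatment, the form lists no 24-hour visit. The visit schedule and the SOFA rule do not fit together.
4. **What a patient treated only with IHD has.** SOFA at admission and before ICU discharge, with none between. The discharge score is of no use as a baseline.
5. **What can be rebuilt at time 0.** PaO2, FiO2, platelets, creatinine, urine volume, blood pressure and vasopressor doses are listed for every modality without a restriction to 24 hours. Bilirubin and a consciousness score are not listed. Taking SOFA in its usual form, which needs both, the full score cannot be derived from the listed fields.

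**The case against.** The strongest reply is that severity at RRT start is largely captured. Time 0 on every form, IHD included, takes oxygenation, platelets, creatinine, urine volume, blood pressure and vasopressors. Step 2 adds RIFLE class and dated triggers. The delay from ICU admission to RRT can be computed from recorded dates. Admission SAPS II, itself a predictor in the cited cohort, is collected. The choice of adjustment variables may belong to an analysis plan that is not shown, and the article names no analysis that requires a composite score at RRT start. Table 1, which guides completion of the forms, is also not shown.

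Much of this stands, and it rules out several stronger readings.

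- A reader might infer that severity at entry is never recorded. The time 0 fields and step 2 show otherwise.
- A reader might infer that no patient has a valid entry severity. Where RRT starts soon after ICU admission, the admission scores lie close to entry. The article gives no distribution of that interval, and entry at RRT start is itself an inference.
- A reader might take the cited cohort's share of intermittent RRT, 233/587 = 39.7%, and conclude that 0.397 × 162 ≈ 64 patients would have no on-treatment SOFA. That share counts first-choice modality in another cohort, not patients treated only with IHD here. A patient who later moves to continuous RRT gets a new form and, if treatment lasts, a 24-hour SOFA.
- A reader might call the gap differential by modality. The missing time 0 score affects all modalities alike; only the on-treatment SOFA differs, and that score is a poor adjustment variable anyway.

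The reply does not remove the core. An analysis plan can choose among collected variables but cannot supply ones that were not collected. The SOFA rule and the IHD visit schedule are both stated explicitly and do not agree.

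**Conclusion.** The point holds in a limited form. No composite severity score is scheduled at RRT start for any modality. The first SOFA after the Admission form is taken after exposure to the delivered dose has begun and is not reached if treatment ends before 24 hours. The SOFA field on the IHD form cannot be completed as scheduled.

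The consequence is a weaker adjustment of the relation between dose and mortality, not an impossible one: partial adjustment with the time 0 variables remains available. The schedule omits the time 0 score for all patients. The number for whom the admission score is materially out of date, and the number treated only with IHD, cannot be derived from the article.

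This rests on two assumptions: that the electronic forms follow the printed rules, and that SOFA is used in its usual form. The change is worth making, though the study does not stand or fall by it.

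**What to change.** In the additional fields for the step 3 forms, request SOFA at assessment time 0 of the first RRT on every modality form, IHD included, and at 24 hours and its multiples on the continuous forms. Add the items missing at time 0, such as bilirubin and a consciousness score. This also removes the mismatch on the IHD form.

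State that the time 0 SOFA is the pre-exposure severity measure when delivered dose is related to mortality, used alongside admission SAPS II and not in place of it.

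The cost is one rule in the electronic form and a few extra routine fields once per patient, since most of the needed variables are already due at time 0. It changes data collection only, not patient care. The change is cheapest before official recruitment, for example during the 2 months each centre has to become familiar with the forms. Later, the missing items would have to be retrieved from patient records.

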**Methods:**

DO-RE-MI is an observational, multicentre study conducted in ICUs. The primary end-point will be the delivered dose of dialysis, which will be compared with ICU mortality, 28-day mortality, hospital mortality, ICU length of stay and number of days of mechanical ventilation. The secondary end-point will be the haemodynamic response to renal replacement therapy, expressed as percentage reduction in noradrenaline (norepinephrine) requirement. Based on the the sample analysis calculation, at least 162 patients must be recruited. Anonymized patient data will be entered online in electronic case report forms and uploaded to an internet website. Each participating centre will have 2 months to become acquainted with the electronic case report forms. After this period official recruitment will begin. Patient data belong to the respective centre, which may use the database for its own needs. However, all centres have agreed to participate in a joint effort to achieve the sample size needed for statistical analysis.

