If we are to understand how dialysis doses are actually delivered in routine clinical practice in ICUs, an observational clinical study is needed to confirm how, to what extent and with what clinical indication the different modalities of RRT are administered. With this in mind we have initiated the DOse REsponse Multicentre International collaborative initiative (DO-RE-MI) trial. The primary end-point of DO-RE-MI is mortality (ICU mortality, 28-day mortality and hospital mortality), and the secondary end-point is the haemodynamic response to RRT, expressed as percentage reduction in noradrenaline (norepinephrine) requirement to maintain blood pressure.

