#### Secondary end-point

Based on data from one participating center (Milan Niguarda), approximately 20% of all RRT-treated patients have high noradrenaline requirements. A sample size of 27 patients will have 80% power to detect a difference in means of 0.295 (e.g. a mean of 2.5 μg/kg per min, assuming a standard deviation for differences of 0.600, using a paired t-test with a 0.05 one-sided significance level). Therefore, a minimun of 135 patients should be enrolled. Assuming a 20% dropout rate, the minimum number of patients to be recruited is 162.

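### The secondary end-point is declared as a percentage reduction in noradrenaline but tested and powered as an absolute change, and the CRF line that supplies it leaves the time basis of the dose open

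*Protocol article*

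**What the plan says.** **Declared end-point.** The Abstract (Methods) gives the haemodynamic response as the secondary end-point, "expressed as percentage reduction in noradrenaline (norepinephrine) requirement". The Introduction repeats it: "the secondary end-point is the haemodynamic response to RRT, expressed as percentage reduction in noradrenaline (norepinephrine) requirement to maintain blood pressure".

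**Sizing.** The Secondary end-point section of the Statistical analysis states: "A sample size of 27 patients will have 80% power to detect a difference in means of 0.295". It adds "a mean of 2.5 μg/kg per min" as an example and continues "assuming a standard deviation for differences of 0.600", with a paired t-test at a one-sided 0.05 level. It takes about 20% of RRT patients to have high noradrenaline requirements. This leads to 135 enrolled and, with 20% dropout, 162 recruited. The Abstract gives 162 as the study's minimum recruitment.

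**Data capture.** The fields common to all modality-specific CRFs (step 3) include a line headed "Vasopressor administration (milligrams of vasopressors/previous 24 hours". Under it the noradrenaline entry reads "noradrenaline (μg/kg per min", as do adrenaline, dobutamine and dopamine in the same unit. Two other agents on the line are "vasopressin (units/previous 24 hours), terlipressin (mg/previous 24 hours".

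**Assessment times.** Intermittent haemodialysis is recorded at 0 h, 4 h and treatment end. For CVVH, CVVHD and CVVHDF the 1, 3, 6 and 12 h assessments are optional, while 24 h and its multiples are mandatory.

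**The concern.** Two separate faults bear on the same end-point.

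The first concerns scale. A percentage reduction and an absolute reduction in μg/kg per min are different random variables with different standard deviations. A power statement for one says nothing about the other unless the baseline dose is the same in everyone or the SD on the second scale is given. Neither is stated. Because the 162 in the Abstract derives from this calculation, the study's recruitment minimum rests on a quantity that is not the declared end-point.

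The second concerns measurement. The heading asks for a cumulative amount, not indexed to weight, over the previous 24 hours. The noradrenaline field asks for a weight-indexed rate. The heading's unit fits only terlipressin. The rate field has no time basis of its own, and the only one on the line is the 24-hour look-back. A current rate and a 24-hour average rate have the same unit and the same plausible range, so no range check would separate them. At an early assessment a 24-hour average consists mostly of time before RRT began, which would understate the size of the response.

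**Working it through.** **1. Reproduce the plan's figure.** Inputs from the Secondary end-point section: difference 0.295, SD of differences 0.600, one-sided α = 0.05, paired t-test.

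- Standardised effect: 0.295 / 0.600 = 0.49.
- Power from the noncentral t distribution with n − 1 degrees of freedom and noncentrality (0.295 / 0.600) × √n: 0.786 at n = 26 and 0.8003 at n = 27.
- The smallest n with at least 80% power is 27, as stated.
- Enrolment: 27 / 0.20 = 135. The stated 162 is 135 × 1.2. (Whether that is the right allowance for dropout is a separate matter.)

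The sizing is therefore sound for an absolute change in μg/kg per min.

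**2. What it implies for a percentage.** Take 2.5 μg/kg per min as the baseline mean (an assumption, since the text gives it only as an example).

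- 0.295 / 2.5 = 11.8%.
- 0.600 / 2.5 = 24 percentage points. This is the SD of the percentage change only if every patient starts at 2.5.

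The plan gives no SD for percentage change, so power on the declared scale cannot be derived. For a mean reduction of 11.8%, one-sided 0.05:

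| Assumed SD of percentage change (points) | Power at n = 27 | n for 80% power |
|---|---|---|
| 20 | 0.91 | 20 |
| 24 | 0.80 | 27 |
| 30 | 0.64 | 42 |
| 40 | 0.44 | 73 |

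Only an SD of about 24 points returns the plan's 27. The true figure could lie on either side.

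**3. What a 24-hour look-back would do to the measured change.** Assume a step change of 0.295 at RRT start, a constant rate before and after it, and entry of the average over the previous 24 hours. The recorded change at hour h is 0.295 × h / 24.

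| Assessment | Recorded change (μg/kg per min) |
|---|---|
| 4 h (intermittent haemodialysis) | 0.295 × 4/24 = 0.049 |
| 6 h (optional, continuous) | 0.295 × 6/24 = 0.074 |
| 12 h (optional, continuous) | 0.295 × 12/24 = 0.148 |
| 24 h (mandatory, continuous) | 0.295 |

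**4. Does that cost power?** In this scenario each patient's own change is multiplied by the same h/24, so the SD shrinks with the mean. At 4 h the SD becomes 0.600 × 4/24 = 0.100, the standardised effect is 0.049 / 0.100 = 0.49, and power at n = 27 stays at 0.80. Holding the SD at 0.600 instead would give 0.11, but nothing in the plan supports diluting the mean and not the spread. What is shown is attenuation of the estimate.

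**5. The two units on the line.** μg/kg per min converts to mg per 24 h by weight × 1440 / 1000 = weight × 1.44. At an assumed 60, 80 and 100 kg the factor is 86.4, 115.2 and 144. It is constant within a patient, so it cancels from a within-patient percentage when the same unit is used before and after.

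**The case against.** The case for leaving the text alone has real force. The noradrenaline field carries its own explicit unit, the same one used in the sizing. The heading cannot govern the whole line, because vasopressin beneath it is in units. The field label is therefore the natural instruction, and a percentage can be computed from paired rates in μg/kg per min. The article lists CRF fields and does not show the form itself. In the continuous modalities a 24-hour look-back at 0 h lies wholly before RRT and at 24 h wholly after it, so that contrast is undiluted under a step change. The Materials and methods section also provides a person responsible for data quality and a correction route for overt inconsistencies.

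These arguments rule out three stronger readings that a reader might infer:

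- *That centres will enter different quantities.* The field's own unit makes this a risk, not a certainty. The percentage-versus-absolute mismatch has no bearing on what is typed in.
- *That power falls from 80% to about 11%.* This dilutes the mean but not the SD. Nor does any section fix 4 h as the time at which the end-point is assessed.
- *That a unit mix-up distorts the end-point by a factor of about 115.* A consistent swap cancels in a within-patient percentage, and a value such as 2.5 × 115.2 = 288 in a field labelled μg/kg per min would stand out.

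Two things survive. The scale mismatch is untouched by any of this. The time basis also remains unstated: a 24-hour average does not look wrong on inspection, and intermittent haemodialysis has no mandatory 24 h assessment to fall back on.

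**Conclusion.** The point holds in two parts.

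First, the stated 80% power with 27 patients, and the 135 and 162 derived from it, belong to an absolute change of 0.295 μg/kg per min and not to the declared percentage reduction. This follows from the text alone. How far power on the percentage scale differs from 80% cannot be said. The range of 0.91 to 0.44 rests on assumed SDs of 20 to 40 points and a baseline mean of 2.5.

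Second, the CRF heading contradicts the noradrenaline field and leaves the time basis open. If 24-hour averages are entered, a step change of 0.295 reads as 0.049 at 4 h and 0.148 at 12 h, with no attenuation at 24 h. That rests on a step change with stable rates on either side. It affects the 4 h assessment of intermittent haemodialysis and the optional early assessments of the continuous modalities. No loss of power is established.

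This is a fault in a secondary end-point that should be corrected. It does not touch the primary analysis.

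**What to change.** **CRF.** Remove the heading in mg per previous 24 hours for the infused catecholamines, and define the noradrenaline field as the infusion rate in μg/kg per min at the assessment time. Agents recorded as 24-hour totals keep their own labels.

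**End-point.** Declare the absolute within-patient change in μg/kg per min as the tested secondary end-point. This matches the existing paired t-test and power statement, and the percentage reduction can then be reported descriptively. If the percentage is kept as the tested quantity, say that the 80% power does not apply to it, and recompute with a stated SD for percentage change. A log ratio relabelled as a percentage would not avoid this: the plan gives no SD on that scale, and the ratio is undefined for a patient whose noradrenaline reaches zero.

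**Cost.** The preferred option needs one CRF label and one sentence, applied consistently in the Abstract, the Introduction and the Secondary end-point section, with no change to the sample size. Keeping the percentage also needs an SD from pilot data and a new calculation. The label is best settled before recruitment, because a closed CRF can be corrected only on written request.
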